**13) Disclosure of data to the patients**

When a patient requests, only data of the patient will be disclosed after the completion of all tests and key open.

**14) Expected period of the Clinical trial**

From the ethical committee approval in 2005 to June 2008.

**VI Adverse events**

1. **Actions taken to handle adverse events**

When an adverse event occurs in a patient, and the event is judged as requiring treatment by the investigator or subinvestigator, the best treatment will be provided to the patient. The investigator will promptly report it to the efficacy and safety committee. Since the investigator cannot judge whether the patient belongs to the active drug or placebo group at the time of the occurrence of the adverse event, the efficacy and safety committee will open the key code allocation table distributed before study initiation by the person responsible for test drug allocation to identify whether the patient is treated with the active drug or placebo, and judge the possibility of causal relationship between the adverse event and ghrelin. When the investigator or subinvestigator judges that continuation of the trial is difficult due to the adverse event, the trial will be discontinued, and the patient will be followed until recovery to the original condition. Regarding the laboratory test values, blood pressure, and pulse rate, values judged as abnormal with clinical significance by the investigator or subinvestigator will be handled as adverse events.

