**Efficacy and safety committee**

Efficacy and safety committee appropriately evaluates adverse events. The committee manages the key code allocation table separately from Investigational drug controller and opens the key, as needed.

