**8) Safety Assessments: All evaluation will be performed under the blinded condition**

(a) Serious adverse event

When a serious adverse event (including acute exacerbation and infections) occurs, the investigator will promptly reports the name of the adverse event, date of administration initiation, onset date, treatment, and outcome at the time of the description to the study director. The trial will be discontinued when the study director judges as continuation is difficult. The study director will investigate the causal relationship with the allocated drug and follow the patient until his/her recovery as much as possible.

(b) Clinical examination for safety assessments (Blood tests)

Haematology and Biochemistry are to be measured before the administration; Weeks 1, 2 and 3 after start of the administration**;** Week 7 after start of the administration, i.e., 4 weeks after the completion of the administration, as well as at any time if clinically indicated**.**

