**2) Adverse event definition**

Adverse events represent all unfavorable events (including abnormal laboratory test values) which develop when the test drug is administered regardless of the presence or absence of causal relationship with the test drug. Adverse events for which causal relationship with the test drug cannot be ruled out will be handled as adverse drug reactions.

Among adverse events, a serious adverse event is defined as any experience of following outcomes:

1. Death.
2. Requires inpatient hospitalization or prolongation of existing hospitalization.
3. Results in a disability (Dysfunction interfere with daily life).
4. An immediate risk of death (i.e., “life threatening”)
5. A risk of disability (i.e., Important medical events that may not result in death, be

life-threatening or require hospitalization, and that, based upon appropriate medical judgment, may jeopardize the patient and may require intervention to prevent one of the outcomes listed above.

Adverse events meeting the following conditions other than serious events are defined as “significant adverse events”.

1. Markedly abnormal variation of laboratory test values
2. Events resulting in discontinuation of the trial

(c) Causal relationship with the test drug (judged as the 2 categories below)

i) No causal relationship: The reason for the development of the adverse event is clear and rules out the causal relationship.

ii) Causal relationship cannot be ruled out: The reason for the development of the adverse event is unclear and cannot rule out the causal relationship, or the reason can be judged as being due to the test drug.

The severity of adverse events will be classified and recorded as follows:

1. Mild: Events are usually transient and do not impair daily living activities.
2. Moderate: Events do not impair daily living activities but are of sufficient discomfort (discomfort accompanies activities).
3. Severe: Events completely impair daily living activities (normal activities are difficult).

Serious adverse events will be handled as follows:

1. Investigators prepare a respirator and drugs for emergency, such as adrenaline and noradrenaline, to treat test drug-induced anaphylactic shock.
2. Staff of each institution engaged in the trial will appropriately supports the actions.

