3. The investigator will open the emergency key of the patient as needed, and quickly inform it to the head of the institution and the Ethics Committee of National Cerebral and Cardiovascular Center by submitting a serious adverse event report.

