**IX Statistics Analyses**

**1)** **Statistics Analyses**

Statistical analysis of this clinical study will be performed by statisticians at the Data Center.

1. **Safety**

Similarity of the following items to the findings obtained at other institutions will be investigated:

a) The incidence of each adverse event will be calculated.

b) Regarding adverse events for which the causal relationship with the test drug cannot be ruled out,

the incidence of each adverse event will be calculated.

c) Regarding serious adverse events (such as death), the incidence will be calculated.

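### The committee opens the treatment code before judging whether a treated adverse event is related to ghrelin, contrary to the stated blinded safety evaluation; this can bias the adverse drug reaction incidence

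*Protocol*

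**What the plan says.** Section VI, item 1 (Actions taken to handle adverse events) deals with events that the investigator or subinvestigator judges to need treatment. The investigator reports the event. Because the investigator does not know the arm, "the efficacy and safety committee will open the key code allocation table distributed before study initiation". The purpose is to learn whether the patient is being "treated with the active drug or placebo, and judge the possibility of causal relationship between the adverse event and ghrelin".

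Other parts of the protocol bear on the same step:

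- The heading of section V.8 (Safety Assessments) states: "All evaluation will be performed under the blinded condition". Within that section, for serious adverse events: "The study director will investigate the causal relationship with the allocated drug".
- Section III, Efficacy and safety committee: "The committee manages the key code allocation table separately from Investigational drug controller and opens the key, as needed".
- Section VI.2 (Adverse event definition): "Adverse events for which causal relationship with the test drug cannot be ruled out will be handled as adverse drug reactions". It offers two causality categories, excluded and not excluded. At its end, for serious events: "The investigator will open the emergency key of the patient as needed".
- Section IX, Safety, item b) calculates an incidence: "Regarding adverse events for which the causal relationship with the test drug cannot be ruled out". Items a) and c) calculate the incidence of each adverse event and of serious adverse events.

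**The concern.** Section VI.1 makes knowledge of the arm an input to the causality judgement. The step is routine for the events it covers, since the only reason given is that the investigator cannot know the arm. An assessor who knows that a patient received saline has a ready reason to say that an unexplained event is not due to ghrelin. The same assessor has no such reason for an identical event on ghrelin. A difference in adverse drug reactions could then appear with no difference in the events themselves.

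The incidence of adverse drug reactions is one of three planned safety results, and safety is a stated objective of the trial. The loss could not be repaired later, because no analysis plan can recover a blinded judgement that was never recorded.

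**Working it through.** The protocol states no figure on this point, so there is nothing to reproduce. The check compares the sections and then gives an illustration of size.

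**1. Order of steps.** In section VI.1 the code is opened, the arm is identified, and relation to ghrelin is judged. No seriousness threshold or clinical need limits this. Section III is softer and lets the committee open the key when needed.

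**2. Conflict.** Section V.8 puts all safety evaluation under blind and itself includes a causality investigation, by the study director for serious events. Causality is therefore part of what that section calls blinded. A serious event that needs treatment falls under both sections, with two assessors and two blinding states.

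**3. What is judged.** Section VI.1 asks about ghrelin. Section VI.2 and section IX b) ask about the test drug. Section IV.1, on identification of test drugs, lists the control as well as the active drug. The two questions coincide on ghrelin but can differ on placebo.

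**4. Link to the analysis.** Section IX b) uses a causality judgement but does not name its source. For treated events that are not serious, the committee is the only causality assessor named. For serious events both the study director and the committee are named.

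**5. Illustration.** Inputs:

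- n = 30 per arm (Summary, item 9).
- p = proportion of patients with a treated event whose relation a blinded assessor could not exclude. This is assumed equal in both arms (no drug effect), from 10% to 40%.
- s = share of such placebo events still classed as not excluded once the arm is known. This is assumed, from 0 to 1.

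Expected reactions are 30 × p on ghrelin and 30 × p × s on placebo. The false difference in incidence is p × (1 − s).

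| p | Blinded (s = 1) | s = 0.5 | s = 0 |
|---|---|---|---|
| 10% | 3 v 3 | 3 v 1.5 | 3 v 0 |
| 20% | 6 v 6 | 6 v 3 | 6 v 0 |
| 30% | 9 v 9 | 9 v 4.5 | 9 v 0 |
| 40% | 12 v 12 | 12 v 6 | 12 v 0 |

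At p = 20% the false difference is 0.20 × (1 − 0.5) = 10 percentage points if half the placebo events stay counted, and 0.20 × (1 − 0) = 20 points if none do.

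**6. What is untouched.** Section IX a) and c) do not use causality, so this route cannot bias them.

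**The case against.** The strongest reply is that the protocol never says the committee's judgement is the one tabulated. Sections VI.2 and IX b) ask about the test drug, which on the wording of section IV.1 can include the control, and an event is excluded there only if its cause is clear. A placebo event could therefore still be counted. Only events needing treatment clearly reach the committee. The reactions reported in the two pilot studies (Background, Previous clinical studies) were mild, so many events may never come to it. All of this stands, and it makes the bias conditional. It does not remove the conflict between sections V.8 and VI.1, and the silence on whose judgement counts is part of the defect.

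Four stronger readings might be inferred, and the documents do not support them:

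- *Placebo reactions are forced to zero.* That needs the committee's judgement to be tabulated and every unexplained placebo event to be reclassified. Neither is stated.
- *The trial would show a significant false difference.* Fisher's exact test on 6/30 v 0/30 gives p = 0.024, but on 3/30 v 0/30 it gives 0.24. The rates are assumed, and section IX plans incidences for safety, with no test between arms.
- *SGRQ and 6-minute walk distance are biased because codes are broken before they are measured.* The committee opens the code. Section VI.1 does not say that the investigator, patient or outcome assessor is told, and section V.7 keeps efficacy assessment double-blind.
- *Any code opening during the trial is an error.* Access in an emergency or when needed is a separate matter. The fault is the routine opening before causality is judged.

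**Conclusion.** The point holds in a conditional form and should be fixed. Sections V.8 and VI.1 contradict each other on whether causality is judged blind, and for serious events also on who judges it. Followed as written, section VI.1 yields a judgement made with knowledge of the arm.

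Where that judgement feeds section IX b), the incidence of adverse drug reactions would be biased between arms, with placebo understated relative to ghrelin. The size is p × (1 − s) and cannot be fixed from the protocol, which gives neither quantity. With 6 of 30 patients per arm affected and no drug effect, the result could lie anywhere from 6 v 6 to 6 v 0. The conclusion is limited to treated events that reach the committee. No effect on the primary outcomes or on the other two safety incidences is shown.

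**What to change.** Reconcile sections V.8 and VI.1 as follows:

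- Causality with the test drug, not with ghrelin, is recorded under blind in the two categories of section VI.2 before any code is opened. Name the assessor for serious and for other events.
- Section IX b) states that this blinded judgement is the one tabulated.
- Any code opening by the committee (section III) or in an emergency (end of section VI.2) is kept separate from that judgement. The date, the reason and the persons informed are recorded. The blinded entry is not changed afterwards, and a later judgement made with the arm known is stored as a separate item. Emergency access to the code is not restricted by this.

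The cost is protocol wording and one dated field on the adverse event record. No extra patients, visits or staff are needed.

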**2) Adverse event definition**

Adverse events represent all unfavorable events (including abnormal laboratory test values) which develop when the test drug is administered regardless of the presence or absence of causal relationship with the test drug. Adverse events for which causal relationship with the test drug cannot be ruled out will be handled as adverse drug reactions.

Among adverse events, a serious adverse event is defined as any experience of following outcomes:

1. Death.
2. Requires inpatient hospitalization or prolongation of existing hospitalization.
3. Results in a disability (Dysfunction interfere with daily life).
4. An immediate risk of death (i.e., “life threatening”)
5. A risk of disability (i.e., Important medical events that may not result in death, be

life-threatening or require hospitalization, and that, based upon appropriate medical judgment, may jeopardize the patient and may require intervention to prevent one of the outcomes listed above.

Adverse events meeting the following conditions other than serious events are defined as “significant adverse events”.

1. Markedly abnormal variation of laboratory test values
2. Events resulting in discontinuation of the trial

(c) Causal relationship with the test drug (judged as the 2 categories below)

i) No causal relationship: The reason for the development of the adverse event is clear and rules out the causal relationship.

ii) Causal relationship cannot be ruled out: The reason for the development of the adverse event is unclear and cannot rule out the causal relationship, or the reason can be judged as being due to the test drug.

The severity of adverse events will be classified and recorded as follows:

1. Mild: Events are usually transient and do not impair daily living activities.
2. Moderate: Events do not impair daily living activities but are of sufficient discomfort (discomfort accompanies activities).
3. Severe: Events completely impair daily living activities (normal activities are difficult).

Serious adverse events will be handled as follows:

1. Investigators prepare a respirator and drugs for emergency, such as adrenaline and noradrenaline, to treat test drug-induced anaphylactic shock.
2. Staff of each institution engaged in the trial will appropriately supports the actions.
3. The investigator will open the emergency key of the patient as needed, and quickly inform it to the head of the institution and the Ethics Committee of National Cerebral and Cardiovascular Center by submitting a serious adverse event report.

**VII Ethical conduct of the study**

1) The study will be conducted in conformity with the ethical principles of the Helsinki Declaration and the study protocol after examination and approval by the Ethics Committee of each institution.

2) **Merits and demerits of the subjects**

a) Merits

Improvement of exercise tolerance and energy metabolism by ghrelin may be expected in the active drug group. Pulmonary rehabilitation performed in both active drug and placebo groups may improve dyspnea and exercise tolerance.

b) Demerits

Improvement of exercise tolerance and energy metabolism by the drug cannot be expected in the placebo group. Since the above merit expected in the active drug treatment group has not been established, the patients will be involved as collaborators for the study.

3) **Consent**

a) Preparation of explanatory document

(1) Investigators will prepare explanatory document to obtain consent from subjects to

participate in the study. The document will be revised as needed. The explanatory document must contain the items presented in b).

(2) The prepared or revised explanatory document is to be approved by the Ethics Committee

of each institution before the use.

b) Descriptions in the explanatory document

The explanatory document is to contain the following items:

(1) The objective of the clinical study is research.

(2) Objective of the clinical study

(3) Study method (inclusion criteria of subjects)

(4) Planned period of subject participation in the study

(5) Planned number of subjects participating in the study

(6) Expected risks and inconveniences (When no merit is expected for subjects, it must be informed to the subjects.)

(7) The presence or absence of other treatment methods and expected important merits and risks of these when patients are selected for the subjects

(8) Compensation and treatment that subjects can receive when health damage related to the clinical trial occurs.

(9) Subjects participate in the clinical trial by their own will and can reject or withdraw the participation any time. They will not be handled disadvantageously or lose benefit that they should receive due to rejection or withdrawal of the participation.

(10) When information which may influence subjects’ will to continue participation is obtained, it will be promptly informed to subjects.

(11) Conditions and reasons to discontinue participation in the study

(12) The Ethics Committee can inspect the clinical study records, in which subject’s secrecy will be kept. Sign and sealing or signature in the consent form by subjects permits inspection of their clinical study records.

(13) Secrecy of subjects will be kept when the study results are published.

(14) Content of payment when subjects have to pay for an expense.

(15) Content of payment when subjects receive payment (agreement on calculation of payment)

(16) Name, occupation, and contact address of the investigator or subinvestigator

(17) Items obliged to subjects

c) Timing and method of obtaining consent

(1) Investigators explain the clinical trial using the explanatory document and obtain written consent from subjects by their own will after providing them with sufficient time to consider.

(2) Participation based on consent by legal representative is not admitted in this study.

(3) The investigator or subinvestigator who explained the study signs the consent form and fills in the date. When a clinical trial collaborator supplementary explained, the collaborator also signs and fills in the date.

(4) The investigators keep the written consents.

(5) The explanatory document and consent (copy) are handed over to the subjects.

**4)**  **Revision of explanatory document and consent form**

a) When new information which may be related to consent of subjects is obtained during the clinical study period, investigators or subinvestigators will promptly inform it to subjects already participating in the study, confirm their will to continue the participation, and record the communication with the subjects on the information and their will are recorded.

b) Investigators or subinvestigators will revise the explanatory document and consent form based on the information as needed, and acquire approval from the Ethics Committee.

c) The revision will be promptly explained using the revised explanatory document and consent form to subjects already participating in the study, and consent by their own will be obtained.

**5)**  **Compliance with study protocol**

Investigators and subinvestigators will perform the study in conformity to the study protocol.

**6)** **Revision of study protocol**

When the study protocol has to be inevitably revised while the study is progressing, investigators can revise the study protocol as needed. Approval by each Ethics Committee is to be obtained to revise the protocol.

**7)**  **Deviation from the study protocol**

a) Investigator and subinvestigators must not deviate from or change the study protocol without approval based on the prior examination by the Ethics Committee.

b) Investigators and subinvestigators can deviate from or change the study protocol without approval by the Ethics Committee of National Cerebral and Cardiovascular Center to urgently avoid risks of subjects or due to other inevitable medical reasons. The investigator or subinvestigator will promptly report the content and reason of the deviation or change and propose the revision if it is appropriate to the Ethics Committee and obtain approval.

c) The investigator or subinvestigator prepares ‘records of deviation from the study protocol’ describing the contents and reasons of all deviations and changes.

**8)**  **Direct inspection of original documents**

In the survey to confirm proper conduct of the clinical study and reliability of data by a person approved by the Ethics Committee, investigators provide all clinical study-related records including the original documents for direct inspection.

**9)**  **Items related to human right of subjects**

a) Protection of subjects’ privacy is sufficiently considered on publication of the study results and handling of raw data related to the study and consent.

b) Information concerning privacy of subjects disclosed to the Ethics Committee on direct inspection of original documents will be protected by taking all appropriate preventive measures.

VIII **Discontinuation, suspension, or completion of clinical trial**

The criteria of discontinuation and suspension are as follows:

a) Occurrence of ethically or medically inevitable conditions, such as those required to secure subject’s safety

b) Loss of scientific validity to investigate the investigational drug

When the clinical trial is discontinued or suspended, the investigator will promptly notify it to the subject and take appropriate countermeasures. The study director has to report it to the Ethics Committee.

**IX Statistics Analyses**

**1)** **Statistics Analyses**

Statistical analysis of this clinical study will be performed by statisticians at the Data Center.

1. **Safety**

Similarity of the following items to the findings obtained at other institutions will be investigated:

a) The incidence of each adverse event will be calculated.

b) Regarding adverse events for which the causal relationship with the test drug cannot be ruled out,

the incidence of each adverse event will be calculated.

c) Regarding serious adverse events (such as death), the incidence will be calculated.

